**iii. Description of data analysis procedure**

The RCT aims to determine the effectiveness of two different infusion rates of antivenom administration. The primary analysis will be done by intention-to-treat using the chi squared test for the primary outcome (or Fisher’s exact test if appropriate) and for other dichotomous outcomes. The relative risk (and risk reduction)and absolute risk reduction (with 95% confidence intervals) will also be calculated. For the outcomes (mainly the primary outcome) where the time –to-event is recorded, the log rank test will be used to compare treatment groups.

Analysis of trends in treatment effect for factors ‘initial dose of antivenom’ and ‘use of antivenom prior to hospital admission’ will also be performed using statistical modeling techniques.

Admission blood samples will be retrospectively analysed to confirm the identity of the snake. The primary analysis will then be repeated to correct for this.

The main hypothesis is that a slower infusion rate of antivenom (10 vials over 2 hours versus 20 minutes) will reduce the rate of all severe allergic reactions following antivenom administration from 50% to 30%.

We also want to determine if the severity of antivenom reaction is inversely related to the severity of envenoming. This will be done by comparing the concentration of venom in patient’s blood (ELISA) to severity of reaction for individual snake species.

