**ii. Detailed description of the research method.**

All patients bitten by a snake will be eligible for the study and will be approached at the time of admission, however they will not formally enter the interventional trial until the decision is made to administer antivenom. All eligible patients will have baseline clinical data collected, including clinical symptoms, signs and a 20 minute whole blood clotting test (20 WBCT). Baseline blood will be collected (see below). When a decision to administer antivenom is made, the patient will be randomized to one of the two parallel treatment arms. Patients in the first treatment group will receive 10 vials of antivenom in 500 ml of normal saline over 20 minutes [alternatively 20 vials of antivenom in 500 ml of normal saline over 40 minutes] Patients in the second treatment group will receive 10 vials of antivenom in 500 ml of normal saline over 2 hrs [alternatively 20 ampoules of antivenom in 500 ml over 4 hours.]

Randomisation will be done by computer in blocks of four (eg. AABB, ABAB etc.) using Microsoft Excel. The computer generated list will be used to randomize pieces of papers to sequentially ordered envelopes with the wording “20 minute infusion” or “2 hour infusion”

Patients will be closely observed for the four hour period following the commencement of administration of antivenom. The patient will be put on a cardiac monitor for this period if possible. For the first hour, HR, BP, RR, oxygen saturation and temperature will be measured every 5 minutes and then every hour for the remainder of the four hours. Patients will be observed for evidence of an allergic reaction using the Brown grading system,(10) including auscultation of the chest. Allergic reactions will be treated as per the current protocol of antivenom reactions with intravenous fluids and 0.5 mg of intramuscular adrenaline into the lateral thigh (or upper arm if not possible).

A 15 mL sample of blood will be taken using a sterile technique (syringe and needle) from each patient.

- 1. The 15mL sample will be divided between one serum (red top tube), one EDTA tube (purple top) and one plasma citrate (blue top) tube.
  2. The serum tube will be spun and the serum aliquoted into 3 portions and frozen.
  3. The citrate plasma tube will be immediately double spun and then aliquoted into two separate tubes and immediately frozen.
  4. The EDTA tube will be spun and aliquoted into two separate containers.

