**How the sample size was determined:**

In two previous studies approximately 50% of patients administered antivenom had a Brown grade 2 or 3 systemic allergic reaction (most commonly hypotension). (4,8) A reduction (absolute) of 20% would be clinically significant and would be sufficient to warrant the use of premedication. In order to detect whether premedication reduces the rate of allergic reactions from 50% to 30%, with a significant level (alpha) of 5% and a power of 80%, a minimum of 103 patients must be recruited to each arm of the trial (i.e. A total of 206 patients). To ensure appropriate recruitment and loss of patients the aim will be to recruit 240 patients.

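### The primary test is valid but unadjusted; one pre-specified analysis using baseline data already collected could gain some precision and would replace a species correction that has no stated method

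*Protocol*

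**What the plan says.** All references are to the protocol.

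- **Primary analysis** (iii. Description of data analysis procedure): "The primary analysis will be done by intention-to-treat using the chi squared test for the primary outcome", with Fisher's exact test as the fallback. Relative and absolute risk reductions with 95% confidence intervals are promised. No covariate or stratification factor is named.
- **Second run** (same section): once admission samples have confirmed the snake's identity, "The primary analysis will then be repeated to correct for this". The method of correction is not given.
- **Question about envenoming** (same section): "We also want to determine if the severity of antivenom reaction is inversely related to the severity of envenoming". It is to be examined through ELISA venom concentration, separately for each species.
- **Baseline data** (ii. Detailed description of the research method): "All eligible patients will have baseline clinical data collected, including clinical symptoms, signs and a 20 minute whole blood clotting test (20 WBCT"), together with baseline blood. Species and venom concentration are assayed from blood later.
- **Allocation** (same section): computer-generated blocks of four. No stratification factor is stated, although the Research Plan lists three hospitals.
- **Sample size** (How the sample size was determined): "a minimum of 103 patients must be recruited to each arm of the trial", to detect 50% v 30%. The recruitment aim is 240.

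**The concern.** When a baseline variable predicts the outcome, an unadjusted comparison leaves the explained variation in the standard error. The interval for the risk difference is then wider than the data in hand allow. A chance difference between arms in that variable also moves the estimate, and neither the described randomisation nor the primary test takes account of it.

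The protocol gives two reasons to think such variables may exist. It intends to correct the primary result for species, and it suspects that venom concentration is related to reaction severity. A third reason is an inference from the outcome definition. Grade 3 rests on low saturation, low systolic pressure, confusion, collapse or loss of consciousness, with no stated requirement for change from the pre-antivenom state. The consent section allows unconscious patients to enter through relatives. Baseline condition could therefore bear on the endpoint.

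At stake is some precision that needs no extra patients, and a clear statement of how species enters the trial's answer.

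**Working it through.** **Inputs from the protocol.** Rates of 50% and 30%, alpha 5%, power 80%, 103 per arm, recruitment aim 240 (120 per arm), and a one-year forecast of 200 (100 per arm). Sidedness is not stated; two-sided is used because it reproduces the stated number.

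**Step 1: reproduce 103 per arm.** With mean rate 0.40,

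n = [1.960·√(2·0.40·0.60) + 0.842·√(0.50·0.50 + 0.30·0.70)]² / 0.20² = [1.960·√0.48 + 0.842·√0.46]² / 0.04 = 93.0.

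Continuity correction: n' = (n/4)·[1 + √(1 + 4/(n·0.20))]² = (93.0/4)·[1 + √1.215]² = 102.8, rounded up to 103. This matches exactly. The trial is sized for the unadjusted test with continuity correction.

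**Step 2: unadjusted power at 103 per arm, without continuity correction.**

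z = [0.20·√103 − 1.960·√0.48] / √0.46 = (2.030 − 1.358)/0.678 = 0.991, so power is 83.9%.

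**Step 3: power with adjustment.** Let rho be the correlation between the outcome and the covariate prediction. The protocol gives no value, so rho is an assumption shown as a range. Adjustment multiplies the variance of the risk difference by (1 − rho²), which is the same as replacing n by n/(1 − rho²). The 95% half-width is 1.96·√(0.46·(1 − rho²)/n).

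| Assumed rho | Effective n for 103 | Power, 100 per arm | Power, 103 per arm | Power, 120 per arm | Half-width at 103 (points) |
|---|---|---|---|---|---|
| 0 | 103 | 82.8% | 83.9% | 89.0% | 13.1 |
| 0.2 | 107.3 | 84.3% | 85.4% | 90.2% | 12.8 |
| 0.3 | 113.2 | 86.2% | 87.2% | 91.7% | 12.5 |
| 0.4 | 122.6 | 88.8% | 89.7% | 93.6% | 12.0 |
| 0.5 | 137.3 | 92.0% | 92.7% | 95.8% | 11.3 |

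At 103 per arm a gain of 5 points needs rho of about 0.37, or about 14% of outcome variance explained (0.37² = 0.137).

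**Step 4: check by simulation.** 4,000 trials per setting, 103 per arm, one normally distributed baseline covariate, logistic model with standardised risk difference:

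| Covariate odds ratio per SD | Unadjusted power | Adjusted power | Variance reduction |
|---|---|---|---|
| 1 | 84.5% | 84.2% | none |
| 1.5 | 84.8% | 85.9% | 4% |
| 2 | 84.4% | 87.6% | 9% |
| 3 | 85.2% | 91.2% | 20% |

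Variance reductions of 4% and 9% correspond to rho of about 0.2 and 0.3, so formula and simulation agree. A useless covariate gains nothing.

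**Step 5: if grade 3 events are rarer.** The sizing section's 50% is for grade 2 or 3 reactions, while the primary outcome is grade 3. With an assumed 30% v 15% and 103 per arm, the same formula gives 73.5% unadjusted, and 77.5% and 80.7% at rho 0.3 and 0.4. Expected events fall from 103·(0.50 + 0.30) = 82 to 103·(0.30 + 0.15) = 46, which limits how many terms a model can carry.

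**The case against.** The strongest reply is that nothing here is wrong. An unadjusted chi-squared test by intention to treat is valid. Its error rate and interval already allow for chance imbalance under randomisation, and 103 per arm was calculated for it. **That stands:** there is no bias and no power shortfall arising from this choice.

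A reader might infer that the protocol expects baseline signs, species and venom concentration to predict reactions. It does not say so. The link to envenoming is posed as a question, concerns venom concentration only, and is to be examined within species. Species appears only as something to correct for. The relevance of baseline signs is an inference from the grade 3 definition.

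A reader might also infer that power already paid for is being lost. The size of any gain rests on a correlation the document does not give. At rho of 0.2 the gain is about 1.5 points at 103 per arm, and at the 240 aim it is smaller still.

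It can also be said that species is already handled by the planned repeat, and that the chi-squared run is plainly the primary one. The second part is a fair reading. The first is only half an answer, because the repeat has no method and could mean restriction, stratification or a model. Stratified randomisation by ELISA species is not a realistic remedy, since species is confirmed retrospectively.

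Finally, a large model would bring its own trouble. Systolic pressure and oxygen saturation are specified for the observation period after antivenom starts and are not named among baseline items. Log concentration is undefined for undetectable venom. Rare species or few events could make the fit unstable. **These limits stand** and shape the fix.

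**Conclusion.** The point holds as a recommended improvement in efficiency and clarity, not as a defect in validity. The protocol fixes an unadjusted primary test and adds a species correction without a method, while pre-antivenom data that may be prognostic are collected anyway. If they are prognostic, adjustment at 103 per arm raises power from 83.9% to about 85 to 87% at rho 0.2 to 0.3 and about 90% at 0.4. The half-width narrows from 13.1 to between 12.8 and 12.0 points over the same range. If they are weak, little or nothing is gained.

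These figures assume the planned rates of 50% and 30%, a two-sided 5% test without continuity correction, and covariates taken only from before antivenom. The missing method for the repeat run needs no assumption: it follows from the text.

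**What to change.** Pre-specify one parsimonious intention-to-treat analysis as primary: a logistic model for grade 3 reaction with treatment arm and a short named covariate list. Report it as a standardised risk difference and relative risk with 95% confidence intervals, so that the measures already promised keep their meaning. State:

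- **Covariates, pre-antivenom only:** hospital, named baseline signs as actually recorded (with the 20 WBCT if wanted), species group, and admission-sample venom concentration. Name systolic pressure or saturation only if the baseline form captures them.
- **Assay rules:** how undetectable and missing results are coded, so that no randomised patient is dropped.
- **Stability rules:** how rare species are pooled, and which terms go first if events are few.
- **Status:** this analysis gives the trial's answer and replaces the run to correct for snake identity. The unadjusted chi-squared test stays as a sensitivity analysis.

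The change is mainly analysis wording, settled before outcome data by arm are seen, and needs no extra recruitment. The costs are a somewhat more complex model and a primary result that waits for the ELISA, which the plan already needs for its repeat run.

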**Research Plan:**

**Study centre**: Base Hospital Chilaw, Anuradhapura, Peradeniya for a period of 12 months. It is an original study, **A randomized, open label, controlled clinical trial.** A total 240 patients will be recruited in this study.

A randomized, double-blind, controlled clinical trial with two parallel groups:

- 10 vials of polyvalent antivenom administered in Normal saline (500ml) over 20 minutes*
- 10 vials of polyvalent antivenom administered in Normal saline (500ml) over 2 hours*

If the patient is administered more than 10 vials then this will be given at the same rate =10 vials over 20 minutes or 2 hours (Although the volume and dilution can be modified for convenience).For example 20 vials given over 40 minutes in 500 ml of Normal saline.

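### The protocol does not say how one blocked list serves three hospitals, and the primary test ignores hospital; the test is valid, but stratifying it by hospital would be a cheap gain

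*Protocol*

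**What the plan says.** - **Sites.** Protocol, *Research Plan*: "Base Hospital Chilaw, Anuradhapura, Peradeniya for a period of 12 months". *Explain recruitment procedures* adds that team members are on duty round the clock in the study hospitals.
- **Allocation.** Protocol, *ii. Detailed description of the research method*: "Randomisation will be done by computer in blocks of four (eg. AABB, ABAB etc.) using Microsoft Excel", and then "The computer generated list will be used to randomize pieces of papers to sequentially ordered envelopes". No stratification factor is named. Nothing is said about whether each hospital has its own envelope series or how one series is divided.
- **Analysis.** Protocol, *iii. Description of data analysis procedure*: "The primary analysis will be done by intention-to-treat using the chi squared test for the primary outcome", with Fisher's exact test as the alternative and a log-rank test where time to event is recorded. The section names initial antivenom dose and prior antivenom use as factors for modelling, and repeats the primary analysis once the snake is identified. Hospital appears nowhere.

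**The concern.** Allocation and analysis should match. If envelopes reach each hospital as whole blocks, the arms are balanced within hospital. A test that ignores hospital then counts between-hospital variation as error that the design has already removed. If one series is shared across hospitals, balance within a hospital is left to chance, and the unadjusted comparison carries that extra noise. The protocol does not say which case applies, and the analysis section provides for neither.

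The stakes are efficiency and slightly wide confidence intervals. They matter only if reaction rates differ between hospitals, for example through snake species or case severity.

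**Working it through.** **1. The plan's own figure.** Inputs from *How the sample size was determined*: 50% v 30%, alpha 5%, power 80%. Sidedness is not stated; two-sided is assumed.

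- n = [1.96·√(2·0.4·0.6) + 0.8416·√(0.5·0.5 + 0.3·0.7)]² / 0.2² = 93.0 per arm.
- With continuity correction: (n/4)·[1 + √(1 + 4/(n·0.2))]² = 102.8, so 103 per arm.

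This matches the stated 103 per arm (206 in total). The point made here does not change that number.

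**2. Size when blocks stay within hospital, by hand.** Assume three equal hospitals and no treatment effect. The true variance of the risk difference is proportional to the mean of p(1−p) over hospitals. The chi-squared test uses p̄(1−p̄) = 0.25.

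| Assumed rates (%) | Mean of p(1−p) | Ratio to 0.25 | 1.96/√ratio | Approximate size |
|---|---|---|---|---|
| 50/50/50 | 0.2500 | 1.000 | 1.960 | 5.0% |
| 40/50/60 | 0.2433 | 0.973 | 1.987 | 4.7% |
| 30/50/70 | 0.2233 | 0.893 | 2.074 | 3.8% |
| 20/50/80 | 0.1900 | 0.760 | 2.248 | 2.5% |

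With 120 per arm at 50%, discreteness alone brings the uncorrected test's exact size to 4.5%. The simulated sizes below should therefore be compared with about 4.5%, not 5%.

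**3. Simulation.** 240 patients in hospitals of 80/80/80, 40,000 trials per cell, two-sided 5%, uncorrected chi-squared v CMH stratified by hospital. The common odds ratio is (0.3/0.7)/(0.5/0.5) = 0.43. Each cell gives chi-squared / CMH, in %. The Monte Carlo standard error is about 0.1 point for size and 0.2 for power.

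| Assumed rates (%) | Blocks within hospital: size | Blocks within hospital: power | One shared list: size | One shared list: power |
|---|---|---|---|---|
| 50/50/50 | 4.4 / 4.4 | 89.5 / 89.2 | 4.5 / 4.9 | 89.4 / 88.8 |
| 40/50/60 | 4.3 / 4.9 | 88.1 / 88.4 | 4.5 / 4.9 | 87.7 / 87.9 |
| 30/50/70 | 3.3 / 4.7 | 83.7 / 85.6 | 4.4 / 4.9 | 82.4 / 85.7 |
| 20/50/80 | 2.1 / 5.0 | 72.5 / 80.6 | 4.5 / 5.0 | 70.2 / 80.3 |

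At 30/50/70 CMH gains 1.9 points with blocks kept within hospital and 3.3 with a shared list. At 40/50/60 it gains 0.4 and 0.2.

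**4. Unequal hospitals (160/60/20).** At 30/50/70 CMH gains 2.0 points (79.9 v 81.9) with blocks within hospital and 2.4 (79.2 v 81.6) with a shared list. One chi-squared size exceeds 5%: 5.3% with a shared list at 30/50/70. Hospital differences do not cause this. The overall rate there is 92/240 = 38.3%, and the exact size at that rate with identical hospitals and 120 per arm is already 5.3%.

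**5. Chance imbalance under a shared list.** The standard deviation of the shift in risk difference due to hospital mix is √[(4/240)·between-hospital variance]. At 30/50/70 the variance is (0.04 + 0 + 0.04)/3 = 0.0267, which gives 2.1 points against a 20-point target. At 40/50/60 it is 1.1 points.

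**The case against.** The strongest reply is that an unadjusted chi-squared test of a randomised binary outcome is valid, so preferring CMH is a matter of efficiency. Adjustment for centre is also often left to a SAP, which is not shown here. The first part stands in full. The second stands in part: this protocol itself names the primary test and its modelling factors, and hospital is not among them.

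The size of the effect is also open to challenge. The 30–80% range in *Background and Justification* runs across antivenom products. It says nothing about three hospitals in one trial, so no spread between sites is documented. At 40/50/60% almost nothing is lost. The planned repeat analysis by snake identity may also absorb part of any hospital difference. All of this stands and keeps the severity low.

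A reader might infer three stronger things that the protocol does not support:

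- **That the list is not split by hospital and the test is therefore conservative.** The protocol is silent on splitting. The two halves also conflict: the test becomes conservative only if allocation is balanced within hospital, while a shared list leaves its size unchanged.
- **That the blocking is broken or wasted.** A shared list still balances the arms overall, and runs of envelopes in multiples of four would keep balance within each site.
- **That chance hospital imbalance biases the result.** It is random error, already covered by the test's nominal level.

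**Conclusion.** The point holds as a modest gap. The protocol leaves open how one blocked list serves three hospitals, and its primary chi-squared and log-rank tests ignore hospital. Neither reading of the allocation makes the test invalid.

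The consequence is a conservative test if blocks are kept within hospital and rates differ, or an ordinary-sized but less efficient test if the list is shared. A material loss needs a hospital spread of about 30/50/70% or wider, which is an assumption with no figure in the documents behind it. In the equal-hospital calculations at 240 patients, chi-squared power falls below the planned 80% only at 20/50/80%. With hospitals of 160/60/20 it is marginally below at 30/50/70% (79.9% and 79.2%). The case for changing the analysis is that it is nearly free.

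**What to change.** **Analysis section (recommended).** Make the primary test a Cochran-Mantel-Haenszel test stratified by hospital. Report the Mantel-Haenszel risk difference and relative risk with 95% confidence intervals. Stratify any log-rank test by hospital. Keep the unstratified chi-squared test as a sensitivity analysis. Hospital is known for every patient, so no extra patients or data are needed. If hospitals do not differ, the power cost is about 0.2 to 0.6 points with equal hospitals, and 0.7 at most (89.6 v 88.8, unrounded difference 0.72) with hospitals of 160/60/20.

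**Randomisation section.** State how envelopes are allotted to hospitals. If each hospital is given its own list and envelope series, vary the block sizes. *Research Plan* calls the trial open label in one sentence and double-blind in the next, and infusions of 20 minutes and 2 hours are hard to disguise. With fixed blocks of four at one site, staff could deduce the last allocations of a block. That would undercut the statement under *Inclusion and exclusion criteria* that allocation cannot be predicted. Separate lists with fixed blocks would therefore carry a real cost, and the analysis change does not depend on them.

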**Subject Selection**

**Participant characteristics:**

Age more than 14 years

Non pregnant

**Explain recruitment procedures:**

Team members will be on 24hrs a day in the study hospitals. They will be notified of any snake bite admissions by the doctor on duty in the OPD or by the medical wards so they can recruit the patients. Chilaw, Anuradhapura, Peradeniya hospitals manage about 500 snake bite patients annually and of these approximately 50% will receive antivenom. Past experience of poisoning trials in Sri Lanka suggest a high recruitment rate (>90% in a trial of anti-digoxin Fab RCT(9)); so we would conservatively estimate 80% patients would be recruited. This means that 200 patients will be recruited over a one year period.

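### The protocol's own accrual projection gives 200 patients in 12 months, short of the 240 it says will be recruited and 6 short of its minimum of 206

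*Protocol*

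**What the plan says.** Three sections of the protocol bear on this point.

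- **Research Plan.** The study runs at three hospitals "for a period of 12 months", and the size is fixed: "A total 240 patients will be recruited in this study".
- **How the sample size was determined.** For 50% versus 30%, with 5% alpha and 80% power, "a minimum of 103 patients must be recruited to each arm of the trial", which makes 206 in total. The target is then raised: "To ensure appropriate recruitment and loss of patients the aim will be to recruit 240 patients".
- **Explain recruitment procedures.** The same three "hospitals manage about 500 snake bite patients annually", and "of these approximately 50% will receive antivenom". A rate above 90% is cited from an earlier Sri Lankan trial, "so we would conservatively estimate 80% patients would be recruited". The section concludes: "This means that 200 patients will be recruited over a one year period".

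The protocol mentions no extension, additional site or other way to close the gap.

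**The concern.** Duration, target and expected accrual are all fixed in the protocol, for the same hospitals, and they disagree: 200 is less than 206, which is less than 240. The increase from 206 to 240 was judged necessary to cover recruitment shortfall and loss, yet the projection supplies none of that margin and does not quite reach the minimum.

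The practical risk is that the sites cannot tell whether recruitment ends at 12 months or at 240 patients. If it ends on the calendar, the trial falls slightly below its own minimum. If it ends on the count, the stated period is too short. The Research Plan calls the trial open label in one sentence and double-blind in the next. If it is open label, settling the end of recruitment while results are accumulating would invite the question of whether those results influenced the decision.

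**Working it through.** **Inputs, all from the protocol.** About 500 bites a year, 50% given antivenom and 80% recruited (Explain recruitment procedures). 12 months and 240 patients (Research Plan). 50% versus 30%, alpha 5%, power 80%, 103 per arm (How the sample size was determined). Allocation is taken as 1:1, from the randomisation in blocks of four. The protocol does not state whether alpha is one- or two-sided.

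**1. Reproduce the projection.** 500 × 0.50 = 250 antivenom recipients; 250 × 0.80 = 200 a year. This matches the stated figure.

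**2. Reproduce the minimum.** With mean proportion 0.40 and two-sided alpha:

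- Without continuity correction: n = [1.960 × √(2 × 0.40 × 0.60) + 0.842 × √(0.50 × 0.50 + 0.30 × 0.70)]² / 0.20² = 93 per arm, 186 in total.
- With continuity correction: n′ = (n/4) × [1 + √(1 + 4/(n × 0.20))]² = 103 per arm, 206 in total. This matches exactly.
- One-sided versions give 74 (uncorrected) or 83 (corrected) per arm, and do not match.

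The protocol's figure therefore rests on a two-sided, continuity-corrected calculation.

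**3. Compare.**

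- Against the target: 240 − 200 = 40, and 40/240 = 16.7%.
- Against the minimum: 206 − 200 = 6, and 6/206 = 2.9%.

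**4. Recruitment rate needed within 12 months.**

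- For 206: 206/250 = 82.4% of antivenom recipients.
- For 240: 240/250 = 96%.
- At 90% recruitment: 250 × 0.90 = 225, still 15 short of 240.

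**5. Time needed at 200 a year.**

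- For 206: 206/200 × 12 = 12.4 months.
- For 240: 240/200 × 12 = 14.4 months.

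**6. Power for 50% versus 30%, everyone analysed.** The corrected version is Φ{[0.20 − 1/n − 1.960 × √(0.48/n)] / √(0.46/n)} with n per arm; the uncorrected version drops the 1/n term. At n = 100 the corrected value is Φ{(0.19 − 0.1358)/0.0678} = Φ(0.80) = 78.8%.

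| Total analysed | Corrected | Uncorrected |
| --- | --- | --- |
| 200 | 78.8% | 82.8% |
| 206 | 80.1% | 83.9% |
| 240 | 86.3% | 89.0% |

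With no losses, stopping at 200 costs about one point against the minimum (80.1 − 78.8 = 1.3) and about seven and a half against the full target (86.3 − 78.8 = 7.5).

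**The case against.** The strongest reply is that this is an optimistic timeline and not a design fault. No calendar stopping rule is written. The 12 months stands beside the list of centres, and 240 is stated both as the number to be recruited and as the aim, so recruiting to the number is a natural reading; on it, power is unaffected. The inputs are approximate, 80% is called conservative, and 206 needs only 82.4%, so a gap of 6 is within rounding. The analysis section names the chi-squared test without a continuity correction, and on the uncorrected calculation 200 patients exceed the 186 required.

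Much of this stands. The shortfall against 206 is slight, and it would be wrong to say that 80% power is plainly lost. The reply does not rescue 240 in 12 months, because even 90% recruitment falls short.

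Three stronger readings that a reader might infer are not supported:

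- **Power near 72%.** This treats 206/240 as a 14% attrition rate, leaving about 172 of 200. The sample size section states no loss rate; 240 is a combined margin for recruitment and loss. The primary outcome is observed in hospital within 4 hours of starting antivenom, and the protocol expects complete follow-up. The only follow-up difficulty it describes concerns serum sickness after discharge, a secondary outcome.
- **200 as an upper limit.** The recruitment section does not say whether the 250 recipients, or the 80%, already allow for age, pregnancy, previous antivenom or unaccompanied unconscious patients. The yield could be lower, but that is not established.
- **15 to 16 months at the stated rate.** The stated rate gives 14.4 months. Reaching 16 requires an assumed further 10% exclusion that the protocol does not give.

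**Conclusion.** The inconsistency is real and lies wholly within the protocol. Its projection of 200 in a year is 40 below the 240 it says will be recruited in a 12-month study, and 6 below its minimum of 206.

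The effect on power is modest and conditional. If recruitment ended at 12 months and all 200 were analysed, power would be about 79% on the basis that gives 103 per arm, or 83% uncorrected, with nothing held back for losses. Any loss or exclusion not already counted would lower this further, but the protocol gives no rate for either, so no firmer figure can be stated.

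The conclusion assumes that the protocol's inputs of about 500, 50% and 80% are taken at face value, and that alpha is two-sided, which is what reproduces 103.

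**What to change.** Choose one of the following and make the sections agree.

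- **Recruit to number.** In the Research Plan and the recruitment section, state that recruitment continues until 240 patients are randomised, expected to take about 14.4 months at the stated rate. Say whether the 250 antivenom recipients are net of the exclusions; if they are not, the expected period is longer. The sample size section then needs no change on this point.
- **Keep 12 months.** In the Research Plan and the sample size section, restate the size as about 200 and the power as about 79% on the continuity-corrected basis, and note that this leaves no margin for losses.

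The cost is a longer stated timeline in the first case, or a slightly lower stated power in the second. Neither needs patients beyond the 240 already planned.
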